## Abstract

**Background:**

Major depressive disorder (MDD) is one of the most prevalent mental health disorders and has a significant societal economic burden. Antidepressants and cognitive behavioral therapy are two primary interventions for the standardized treatment of MDD. However, their weaknesses, such as a low response rate, a high risk of adverse events from medication, and the high cost of cognitive behavioral therapy, have resulted in a need for complementary and alternative medicine (CAM). Among the various therapeutic interventions in CAM, electroacupuncture and moxibustion have been widely used to treat various mental illnesses, including MDD. The aim of this study is to evaluate the feasibility of conducting a full-scale randomized controlled trial to investigate the efficacy and safety of electroacupuncture plus moxibustion therapy for MDD.

**Methods/design:**

We will include patients between the ages of 19 to 65 years with MDD. A total of 30 participants will be recruited, and they will be randomly allocated into two groups at a 1:1 ratio. Patients in the treatment and control groups will, respectively, receive real and sham electroacupuncture/moxibustion treatments, for a total of 20 sessions over 8 weeks. The primary outcome will be the Hamilton Rating Scale for Depression, and the secondary outcomes will be Beck’s Depression Inventory, the Insomnia Severity Index, the State-Trait Anxiety Inventory, the EuroQol 5-Dimension Index, the Measure Yourself Medical Outcome Profile version 2, and electroencephalography. Adverse events will be monitored at each visit to assess safety. All outcomes will be assessed and analyzed by researchers blinded to the treatment allocation.

**Discussion:**

This is a two-armed, parallel-design, patient-assessor blinded, multicenter, randomized, sham-controlled pilot clinical trial. Data will be analyzed before and after treatment and during a 4-week follow-up. The results of the trial will provide a basis for further studies assessing the efficacy and safety of electroacupuncture plus moxibustion treatment for MDD.

**Trial registration:**

Korean Clinical Trial Registry, CRIS-KCT0001810. Registered on 5 February 2016 (retrospectively registered; date of enrollment of the first participant to the trial: 2 December 2015).

**Electronic supplementary material:**

The online version of this article (doi:10.1186/s13063-016-1741-2) contains supplementary material, which is available to authorized users.

## Background

Major depressive disorder (MDD) is one of the most prevalent mental health disorders [1] and is characterized by a depressed mood, feelings of tiredness, anxiety, poor concentration, disturbed sleep, decreased appetite, and loss of interest in pleasure [2]. The lifetime prevalence of MDD is estimated to be 8–12% worldwide [3]. This common psychiatric disorder diminishes quality of life and work productivity, which leads to a significant societal economic burden [1]. MDD is the fourth leading cause of disease burden worldwide, and it is predicted to be the second leading cause by 2020 [4]. In Korea, the lifetime prevalence of MDD was 6.7% as of 2011, which is lower than global estimates [5]. However, this figure is a 67% increase over estimates from 10 years prior (4%), reflecting the general upward trend in MDD [5]. MDD is also a societal burden to South Korea, with the socioeconomic cost of the disorder increasing by 41.5% from 2007 to 2011 [6].

The etiology and mechanisms of MDD are complicated and treatment is not simple [7]. Pharmacological therapy and cognitive behavioral therapy are considered two primary methods of standard treatment for MDD [8]. Although these two modalities have similar effects, pharmacological therapy is more commonly prescribed [9]. The high cost of cognitive behavioral therapy is a main reason that patients avoid this treatment [8]. Pharmacological therapy, however, also has challenges, such as a low response rate (40%) and a high failure rate of remission achievement (70%) during initial treatment as well as a high risk of adverse drug reactions [8].

Because of these limitations, both patients and clinicians have sought other therapeutic options, such as complementary and alternative medicine (CAM) [8]. Patients with neuropsychiatric symptoms tend to use CAM more often and also tend to spend more money on it [10, 11].

In South Korea, there is another critical reason that leads people to prefer CAM. According to a survey, patients are unwilling to visit psychiatric clinics because of social prejudices and the decline in private health insurance [12]. Patients instead pursue therapies, such as CAM, because of these sociocultural issues [12].

A variety of therapeutic interventions are available in CAM. Acupuncture, electroacupuncture and moxibustion are some of the most representative nonpharmacologic therapies, particularly in traditional medicine in East Asia, including South Korea, China, and Japan. China has provided more abundant data than any other country in this field, and according to a report by Woo et al. [13] on the current state of Chinese studies in this area, acupuncture, electroacupuncture, herbal treatment plus acupuncture, and acupuncture plus moxibustion are frequently referred therapeutic modalities for the treatment of MDD.

The mechanisms underlying the therapeutic effect of acupuncture in MDD involve regulation of the hypothalamic-pituitary-adrenal (HPA) axis and stimulation of the prefrontal-limbic system [14, 15]. Systematic reviews and meta-analyses of clinical evidence on this issue, however, have shown that the currently available evidence is insufficient to firmly conclude the effectiveness of acupuncture for MDD [8, 16–18].

A few studies conducted in China have shown the usefulness of acupuncture as an adjunct to antidepressants such as selective serotonin reuptake inhibitors [19–22]. A British research team also demonstrated that standard care plus acupuncture was more effective than standard care alone in improving depression [23]. Another study compared the effect of real and sham acupuncture for patients with MDD taking medication [22]. The results indicated that acupuncture outperformed the sham device in attenuating anxiety and mitigating the adverse effects of antidepressants, but the overall therapeutic response rates between the two groups were not significantly different [22]. It has been reported that electroacupuncture, whether alone [24] or combined with medication [20, 25], outperforms antidepressant monotherapy in improving depressive conditions.

Some studies have indicated that acupuncture plus moxibustion therapy is superior to sham acupuncture [26] or to a wait list control [27]. Another study argued that combined therapy compared favorably with acupuncture alone for MDD patients taking antidepressants [28]. Although only a few studies regarding the effect of electroacupuncture plus moxibustion have been published, their results indicate that this combined therapy may be a potential intervention for MDD. Based on the current state of knowledge described above, the present pilot clinical trial was designed to provide a foundation for further studies to confirm the utility of electroacupuncture interventions for patients with MDD.

The aims of this study are to explore the efficacy and safety of electroacupuncture plus moxibustion therapy for MDD and to create a foundation for evaluating the feasibility of using these treatments in a full-scale randomized controlled trial (RCT).

## Methods/design

### Design

This is a two-armed, parallel-design, patient-assessor blinded, multicenter, randomized, sham-controlled pilot clinical trial. Two clinical research centers in South Korea will conduct the trial: Daejeon Oriental Hospital of Daejeon University and Kyung Hee University Oriental Hospital at Gangdong.

To recruit participants, flyers, daily local newspapers, and advertisement boards at research centers will be utilized. Potential candidates will visit the research centers for screening assessment and to sign informed consent for trial participation after being informed about the aim and details of the study. Eligible participants will be randomly allocated at a 1:1 ratio to one of two arms: electroacupuncture plus moxibustion (treatment group) or sham acupuncture with mock electrical stimulation plus sham moxibustion (control group). Participants will receive treatment for 8 weeks and then visit the research centers twice during a 4-week follow-up period (Fig. 1).

**Fig. 1 Fig1:**
[figure not shown]
Flow chart of the trial

### Eligibility

Patients with MDD who meet the following criteria will be included:Between 19 and 65 years of ageFulfillment of *Diagnostic and Statistical Manual of Mental Disorders, version 4* (DSM-IV) diagnostic criteria for either first-onset or recurrent MDD with at least one major depressive episode in the 30 days prior to the date of screeningA Hamilton Rating Scale for Depression (HAM-D) score of between 7 and 24 pointsWillingness to participate in the trial and provide written consent

Subjects meeting any of the following criteria will be excluded:Patients at a high risk of attempting suicide (a score of more than 2 points on the third question (Suicide) of the HAM-D and a greater than moderate risk of suicide on the Screening for Depression and Thoughts of Suicide Scale)Patients with fundamental communication problems due to severely unstable mental disordersWomen who are pregnant, lactating, or planning to become pregnantPatients considered by researchers to be inappropriate for participation due to severely abnormal/unstable laboratory test results or vital signsDiagnosis of unregulated hormone disorders that can affect mood (e.g., uncontrolled dysthyroidism)Excessive exposure to major stressful life events within 1 year prior to the date of screening (≤200 points on the Social Readjustment of Rating Scale)People who have undergone any of the following treatments within the specified period before the date of screening:psychotropic drugs, such as antidepressant, antianxiety, mood stabilizing, or antipsychotic agentsnonpsychopharmacological drugs with psychotropic activitypsychotherapy (including cognitive behavioral therapy)electroshock therapy or transcranial magnetic stimulation, orany type of therapeutic intervention of traditional Korean medicine to attenuate MDD
Subjects who have acute inflammation at the planned acupuncture site on the bodyParticipants with bleeding disorders or those currently taking anticoagulantsPatients with a medical history of severe head injury, hemorrhagic or ischemic stroke, or other diseases related to severe physical disability

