### Interventions

The intervention treatment period includes 20 sessions over 8 weeks. The participants will visit the research center three times a week through the first 4 weeks and then twice a week through the last 4 weeks. Licensed Korean medical doctors who have at least 4 years of clinical experience will perform the intervention. Detailed information on acupuncture and moxibustion is provided in Additional file 1 and Table 1.

**Table 1 Tab1:** Schedule for treatment and outcome measurements

Period	S	T									Follow-up	
Visit		1	2	3	4–12	13	14	15–18	19	20	21	22
Week		1	1	1	2–4	5	5	6–7	8	8	9	13
Informed consent	●											
Inclusion/exclusion criteria	●											
Laboratory test^a^	●										●	
Vital signs	●	●	●	●	●	●	●	●	●	●	●	●
Demographic characteristics	●											
Medical history/BMI	●											
SRRS	●											
SDTS	●					●					●	
Random allocation		●^b^										
Change of history		●	●	●	●	●	●	●	●	●	●	●
Treatment		●	●	●	●	●	●	●	●	●		
HAM-D	●	●^b^				●^b^					●	●
BDI		●^b^				●^b^					●	●
EQ-5D		●^b^				●^b^					●	●
ISI		●^b^				●^b^					●	●
STAI		●^b^				●^b^					●	●
MYMOP2		●^b^				●^b^					●	●
EEG		●^b^				●^b^					●	●
Pattern identification		●^b^										
Safety assessment		●	●	●	●	●	●	●	●	●	●	●
Blinding test		●								●		

*S* screening period, *T* treatment period, *BMI* Body Mass Index, *SRRS* Social Readjustment of Rating Scale, *SDTS* Screening for Depression and Thoughts of Suicide, *HAM-D* Hamilton Rating Scale for Depression, *BDI* Beck’s Depression Inventory, *EQ-5D* EuroQol-5 Dimension Index, *ISI* Insomnia Severity Index, *STAI* State-Trait Anxiety Inventory, *MYMOP2* Measure Yourself Medical Outcome Profile version 2, *EEG* electroencephalography

^a^Complete blood count and differential count, blood urea nitrogen, creatinine, aspartate aminotransferase, alanine aminotransferase, total bilirubin, albumin, erythrocyte sedimentation rate, thyroid-stimulating hormone, free thyroxine, human chorionic gonadotropin urine test (only for women in their childbearing years)

^b^Before treatment

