### Sample size

The purpose of this pilot clinical trial is to explore the efficacy and safety of electroacupuncture plus moxibustion therapy for the treatment of MDD. Based on previous literature [40] (mean difference 4.34, standard deviation 3.75) and assuming a dropout rate of 20%, 15 participants will be assigned to each group.

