### Statistical analysis

Statistical analyses will be performed by an independent statistician blinded to group allocation. Intention-to-treat analysis will be primarily applied in addition to per-protocol analysis. A two-sided test will be used with a significance level of 0.05. Multiple imputation will be adopted when datasets are incomplete.

Sociodemographic information will be presented as the mean ± standard deviation or the frequency (%), and data will be analyzed using Student’s *t* test or the chi-square test. The Wilcoxon rank sum test or Fisher’s exact test will be performed when data are not normally distributed. Analysis of covariance (ANCOVA) will be conducted to compare the mean differences in HAM-D scores between the two groups by substituting each group for factors, points acquired at baseline for covariates, and points assessed at week 9 for dependent variables. RM ANOVA will be performed to analyze the mean change in HAM-D score from baseline to the end of the trial. A paired *t* test or Wilcoxon signed rank test will be applied to compare the average changes between scores assessed before and after treatment. The mean differences of other secondary outcome measurements, such as the BDI, ISI, STAI, EQ-5D, and MYMOP2, will be analyzed following the same methodology as that used in the primary outcome measurement.

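### The exclusion for excessive stressful life events is defined by a low score (≤200), so its threshold contradicts its wording

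*Protocol article*

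**What the plan says.** The second list in the Eligibility section of the protocol article opens with "Subjects meeting any of the following criteria will be excluded", so a single item is enough to keep an applicant out. One item begins "Excessive exposure to major stressful life events within 1 year prior to the date of screening (≤200 points". The bracket gives it a numerical definition, which reads in full: "≤200 points on the Social Readjustment of Rating Scale".

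Table 1, under Interventions, marks the SRRS at the screening visit and at no other time. Within this article, then, its only evident use is the eligibility decision. Table 1 gives neither a cut-off nor a scoring direction, and no other section mentions the threshold.

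Trial status says that participants are still being recruited. Trial registration dates the first enrolment to 2 December 2015.

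**The concern.** The item names a high quantity and then defines it by an upper bound. A screener who follows the words and a screener who follows the number would make opposite decisions about almost every applicant.

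What is at stake is the population. The bracket is the only operational definition of this exclusion, and it is a numerical gate into a trial of 30 patients. If the number were followed, the HAM-D results would describe patients with heavy recent life-event exposure, the group that the words set out to exclude. The article presents the pilot as groundwork for a full-scale trial, so the eligibility text should be right before anyone reuses it.

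**Working it through.** No figure in the plan can be reproduced here, because 200 is a fixed threshold and is not derived from anything. The check is to apply the rule as printed and compare the result with the words.

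**Inputs**
- Meeting any one item on the list excludes (Eligibility).
- Target of the item: "Excessive exposure to major stressful life events" (Eligibility).
- Printed threshold: 200 points or fewer (Eligibility).
- Scoring direction: not given in the article. Assumed here: points rise with exposure.

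**Step 1. Classify scores under the printed rule and the two candidate corrections**

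| SRRS score | Printed: excluded if ≤200 | Excluded if ≥200 | Excluded if >200 |
|---|---|---|---|
| 0 | excluded | not excluded | not excluded |
| 50 | excluded | not excluded | not excluded |
| 150 | excluded | not excluded | not excluded |
| 199 | excluded | not excluded | not excluded |
| 200 | excluded | excluded | not excluded |
| 201 | not excluded | excluded | excluded |
| 250 | not excluded | excluded | excluded |
| 300 | not excluded | excluded | excluded |
| 400 | not excluded | excluded | excluded |

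**Step 2. Compare with the words.** Under the printed rule, an applicant with 0 points counts as excessively exposed and one with 400 points does not. Under either correction, the low scores stay eligible and the high scores are excluded, as the words require.

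**Step 3. How complete the inversion is.** Against >200, the printed rule is the exact complement: every score is classified the other way. Against ≥200, the same is true except at exactly 200, which both rules exclude.

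**Step 4. Does the error reach the statistics?** The Sample size section gives "mean difference 4.34, standard deviation 3.75) and assuming a dropout rate of 20%, 15 participants will be assigned to each group". By the normal approximation, with two-sided alpha 0.05 and power of 80% (assumed, since the section does not state it):

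- n per arm = 2 × (1.96 + 0.84)² × (3.75 / 4.34)² ≈ 2 × 7.85 × 0.747 ≈ 11.7, rounded up to 12
- allowing for 20% dropout: 12 / 0.8 = 15, which matches the stated 15 per group

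The SRRS threshold enters neither line. It is also applied at screening, before random allocation at visit 1, and in the same way to both future arms.

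**The case against.** The strongest reply is that the intent is plain from the words, so this is most likely a misprinted sign in a condensed article. The full protocol, CRF and screening form are not shown, and enrolment began before the article appeared. Screening was presumably run from the approved protocol. The rule also acts before randomisation and on both arms alike, so the comparison between groups is sound under either sign.

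Most of this stands, and it limits the point in four ways.

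- A reader might infer that the trial has enrolled only highly stressed patients. The article does not show this; the consequence follows only if the printed sign was used.
- A reader might infer that the sign must become ≥200. The article does not settle that. The bracket could be a mistyped ≥200, or it could be the permitted range (≤200 eligible) carried into the exclusion list, which would make the exclusion >200.
- A reader might want to say what share of applicants would be turned away. The article gives no distribution of SRRS scores, so no share can be stated.
- A reader might supply a reason for the criterion, for example that depression following recent events may resolve by itself. The article gives no reason, and the point does not need one.

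The reply does not remove the contradiction. The article states both the words and the number, in one item of running text, and no other section corrects either of them. This is therefore not a detail left to a fuller document.

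**Conclusion.** The point holds as an internal contradiction in a numerical entry criterion. It rests on one assumption that the article does not state: that a higher SRRS score means greater exposure. Only the opposite scoring would reconcile the words with the number, and nothing in the article suggests it.

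Taken literally, the rule reverses the eligibility decision at every score except possibly exactly 200. The effect would fall on the enrolled population and on how far the results generalise. The randomised comparison, the sample size of 15 per group and the planned analyses are unaffected. Whether any applicant was actually misclassified is unknown from the article. The text needs correcting because it is wrong as written; harm to the trial has not been shown.

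**What to change.** 1. Reverse the inequality in the bracket so that it agrees with the wording. Take ≥200 or >200 from the approved protocol.
2. State in the same item that higher SRRS scores mean greater exposure, once this is confirmed, so that the direction no longer has to be assumed.
3. Confirm from the CRF and the screening log at both centres which sign was applied. Record anyone wrongly included or wrongly turned away as an eligibility deviation.
4. Keep any affected randomised patients in the intention-to-treat analysis, which the Statistical analysis section already makes primary.

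The cost is a one-character correction, one clarifying phrase and a check of the screening log. No calculation or analysis has to be redone.

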### Randomization, allocation concealment and blinding

An independent statistician will generate a randomization schedule using SAS (Version 9.4, SAS institute. Inc., Cary, NC, USA). Fifteen subjects will be assigned to each group through the gender-stratified block randomization method. The randomization list will be sealed in sequentially numbered and gender-marked opaque envelopes, delivered to each research center, and stored in a double-locked cabinet. After a candidate participant who meets the eligibility criteria signs an Informed Consent Form, the practitioner will open the corresponding envelope. After the practitioner checks the group allocation for the subject, the envelope will be stored again in a separate, double-locked cabinet. Allocation concealment will be maintained throughout the trial.

It is impossible to blind the practitioners; therefore, they will be excluded from the assessment procedure. All other researchers, such as assessors and data analysts, will be blinded to the group allocation. To confirm that participant blinding was achieved, after both the first and final treatments, assessors will use a “blinding test” questionnaire to ask participants which type of therapy, real or sham, they thought they had been given.

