### Outcomes

The following outcomes will be assessed by independent assessors blinded to the allocation.

The primary outcome measurement of this study is the mean change of total scores in the HAM-D from baseline to the end of the treatment period (week 9). Since its development in the 1960s, the HAM-D has been considered a standard scale to assess MDD severity. The range of the HAM-D score is 0 to 52, with 0–6 indicating normal, 7–17 indicating mild, 18–24 indicating moderate, and 25 or more indicating severe MDD. We will use the validated Korean version of the HAM-D [32].

Secondary outcome measurements include the average change in the HAM-D (from baseline to weeks 5 and 13). The same version of the HAM-D used for the primary outcome measurement will be applied again. In addition, Beck’s Depression Inventory (BDI), the Insomnia Severity Index (ISI), the State-Trait Anxiety Inventory (STAI), the EuroQol-5 Dimension Index (EQ-5D), the Measure Yourself Medical Outcome Profile version 2 (MYMOP2), and electroencephalography (EEG) will be measured as secondary outcomes.

BDI is a multidimensional questionnaire used to assess the severity of the clinical symptoms of MDD. It includes 21 questions to evaluate patients’ cognitive, emotional, and physiological aspects, and the score can range from 0 to 63 points. A higher score indicates a more severe condition [33].

The ISI is an assessment tool designed to diagnose insomnia and evaluate its severity. The range of the score is 0 to 28, with 0–7 points indicating no clinically significant insomnia, 8–14 indicating subthreshold insomnia, 15–21 indicating moderate insomnia, and 22–28 indicating severe insomnia [34].

The STAI is a questionnaire developed by Spielberger et al. in the 1970s. It includes two subscales to assess state anxiety and trait anxiety. Each subscale has 20 items [35].

The EQ-5D is an instrument developed by the EuroQoL group to measure quality of life in terms of health conditions. It includes five items and uses a Visual Analogue Scale to assess overall health conditions [36].

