As sham interventions for real acupuncture and moxibustion, a mock electrostimulation using a Park sham placebo device and a modified moxibustion to block the heat channel will be applied at nonacupoints unrelated to depression in this study. There may be concerns that the participants may be aware as to which type of treatment they have received because of the difference of numbers and sites of the points used in each group, even though the appearances of therapeutic tools are identical. The development of appropriate sham interventions for acupuncture or moxibustion has been one of the greatest challenges for researchers in this area. There have been several types of sham interventions suggested until now. It is one of the most commonly used types of sham interventions to apply acupuncture needles with a blunt edge and insulated moxibustion at nonacupoints [16–18, 31, 46–48]. No one can say for sure that it is a perfect and faultless method as a sham intervention for acupuncture and moxibustion study. However, to date it is one of the best options that we can choose [48–50].

In this trial, no one is allowed to see the scene of intervention aside from the operator. The participants, therefore, cannot notice anything about the difference of the numbers of sites of the points between groups. Moreover, the blinding test to investigate whether the participants have really noticed the types of interventions that they have received or not will be performed after completing the first and last treatment during the study. The results of the blinding test as well as the efficacy and safety outcomes will be reported.

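### The blinded assessors, the role that rates HAM-D, also collect participants' real-or-sham guesses before every post-baseline rating, and nothing separates the two tasks

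*Protocol article*

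**What the plan says.** All places are in the protocol article.

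- **Randomization, allocation concealment and blinding.** Practitioners cannot be blinded and are kept out of assessment. For the rest: "All other researchers, such as assessors and data analysts, will be blinded to the group allocation". The next sentence reads: "To confirm that participant blinding was achieved, after both the first and final treatments, assessors will use a" blinding-test "questionnaire to ask participants which type of therapy, real or sham, they thought they had been given".
- **Outcomes.** "The following outcomes will be assessed by independent assessors blinded to the allocation". HAM-D is the first outcome listed. Its change from baseline to week 9 is primary; the changes to weeks 5 and 13 are secondary.
- **Table 1.** The blinding test is marked at visit 1 (week 1) and visit 20 (week 8). HAM-D is marked at screening, visit 1 (before treatment), visit 13 (week 5, before treatment), visit 21 (week 9) and visit 22 (week 13).
- **Discussion.** The timing of the test is confirmed: it "will be performed after completing the first and last treatment during the study".

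The article names no other person to collect the guess, no sealed or privately completed form, and no rule that keeps the answer from the HAM-D rater.

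**The concern.** The article gives one role two tasks that should be kept apart. The assessors are to rate HAM-D without information about allocation. They are also sent to ask each participant, twice, what treatment the participant believes was given. The check on participant blinding thus becomes a channel by which allocation-related information can reach the rater.

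The primary outcome is a score that an assessor assigns. If a rater who knows that a participant believes the treatment was sham scores that participant even slightly worse, and such beliefs are commoner in the sham arm, the arms differ for a reason unrelated to treatment. Adjustment for baseline HAM-D in the planned ANCOVA does not remove this, because the baseline rating precedes the first guess and carries none of the shift. The pilot is meant to lay the ground for a full-scale trial, so an inflated difference could be carried forward into its design.

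**Working it through.** **1. The plan's own figure.** Under Sample size the article gives a mean difference of 4.34, a standard deviation of 3.75, 20% dropout and 15 per group. Statistical analysis gives a two-sided 0.05 level. Power is not stated; 80% is assumed here. By the normal approximation:

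n = 2 × (1.96 + 0.84)² × 3.75² / 4.34² = 2 × 7.84 × 14.06 / 18.84 ≈ 11.7, so 12 per group; 12 / 0.80 = 15.

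The stated size reproduces and is not in dispute. The 4.34 serves below only as a yardstick.

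**2. Order of events, from Table 1.**

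| HAM-D rating | Guesses already collected |
|---|---|
| Visit 1, before treatment (baseline) | none |
| Visit 13, week 5 | one (visit 1) |
| Visit 21, week 9 (primary) | two (visits 1 and 20) |
| Visit 22, week 13 | two (visits 1 and 20) |

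The baseline rating is clean. All three post-baseline ratings follow at least one guess, and the primary follows two.

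**3. Could guesses differ by arm?** Under Interventions, active needles enter the skin, are manipulated to *deqi* and carry a current strong enough to be noticed; the moxibustion heat is not blocked. Sham needles cannot penetrate, no current flows, and the heat channel is plugged. The sites also differ: head, chest, hand and forearm points in the active arm, upper arms and legs in the sham arm. A difference in guesses is therefore plausible. The article gives no figure for it.

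**4. Size of the possible bias.** Let s be the number of HAM-D points by which a rater scores a believed-sham participant worse than a believed-real one. Then

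bias = s × [P(guess real | active) − P(guess real | sham)].

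If a fraction c guesses correctly in each arm, the bracket is c − (1 − c) = 2c − 1. Both s and c are assumptions.

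| c | s = 1 | s = 2 | s = 3 |
|---|---|---|---|
| 0.50 | 0 | 0 | 0 |
| 0.65 | 0.3 | 0.6 | 0.9 |
| 0.75 | 0.5 | 1.0 | 1.5 |
| 0.85 | 0.7 | 1.4 | 2.1 |

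As a share of 4.34, the non-zero entries run from 0.3 / 4.34 = 7% to 2.1 / 4.34 = 48%. The bias is also zero whenever both arms guess real equally often, whatever that proportion is, and whenever raters are not swayed (s = 0).

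**The case against.** Several points can fairly be made for the plan.

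- **Same role, not necessarily same person.** The assessors are a plural role in a trial at two centres. The article does not say that whoever asks for the guess also rates that participant, nor whether the questionnaire is spoken or self-completed. The full protocol may settle this. That stands as a limit on certainty. It does not clear the text, which assigns the task to the blinded role and describes no separation.
- **A guess is not the allocation.** A reader might infer that the raters are effectively unblinded. The documents do not support that: a guess informs only as far as guesses are correct, and no rate is given.
- **The question is narrow.** A reader might infer that the test draws out reports of current, heat or needle sensation. The article asks only real or sham. Remarks about sensation could be a by-product but are not an item.
- **The primary rating is at a separate visit.** The second guess is at visit 20 in week 8 and the primary HAM-D at visit 21 in week 9. The week-5 rating comes about four weeks after a guess based on one session. The rater would not have just heard the answer, though it may be remembered or on file.
- **The sham is designed so that both arms guess alike.** The Discussion argues that participants cannot see the procedure and so cannot notice differences in point number or site. If that works, the bias is zero. But being unable to see does not stop a participant feeling penetration, current or heat.
- **It is a 30-patient pilot, and the results of the blinding test will be reported.** Unequal guessing would be visible, exploratory checks would be possible, and the self-reported BDI and the EEG do not rest on a HAM-D rater's judgement. This lowers the stakes, but reported guesses would not show whether raters were swayed by them.

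**Conclusion.** The point holds as a weakness in a stated procedure. The role that the article declares blind and charges with rating outcomes also collects the guesses. All three post-baseline HAM-D ratings, the primary included, come after at least one guess, and no barrier is described. The order of visits is exact; that the same individual does both tasks is the plain reading of a shared role name, not a stated fact.

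The effect on the primary comparison is conditional. It ranges from nothing, if both arms guess alike or raters are unaffected, to about 2 points at the upper end of the assumptions (s = 3, 85% correct in each arm). It would favour the active arm only if guesses lean towards the true allocation and raters score believed-sham participants worse. A reader might infer an established bias; the documents show a route for one and give no figure for its size. The sample size is unaffected. The change is worth making because the exposure is to the primary outcome and the remedy costs very little.

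**What to change.** - Have each participant complete the blinding test alone and seal it in an envelope, or have a coordinator who does no ratings collect it. The practitioner should not collect it: the article keeps practitioners out of assessment, and answers given to the person who delivered the treatment may be coloured by that.
- Keep the answers from the HAM-D assessors until the last HAM-D rating or database lock.
- Instruct participants not to discuss their treatment with the assessor.
- State in the section on blinding who handles the form. If the full protocol already separates the tasks, one sentence saying so is enough.

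With sealing, the second test can stay at visit 20. Moving it after visit 21 is unnecessary: another week of perceived improvement could then shape the guess, and visit 22 would still follow it.

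The cost is a minor change to form handling, with no change to sample size or visits. Recruitment is already under way, so the change protects only ratings still to come; the report should say how guesses were collected before it took effect.
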